### Study Power

Aim 2 analyses will compare study conditions based on family attendance and client outcomes over time, with client (N=60) as the unit of analysis. Assuming α=.05, a total sample size of N=60 (with 30 clients per condition), 3 measurement occasions with a moderate intercorrelation (*r*=0.50), and a moderate effect size of Cohen *d*=0.60, the analysis yields a power of 0.80. A smaller effect size of Cohen *d*=0.50 yielded a power of 0.65, assuming α=.05. These estimates are in line with the impacts seen in the studies on adolescents with ID but not SUD [60,62] and in the studies on adolescents with SU problems treated in usual care [79,94].

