*Aim 2a family attendance* will involve between-condition comparison of treatment sessions attended by family members other than the adolescent. Linear mixed effects (LME) modeling will be used to examine the effect of condition on attendance counts. The model will include fixed effects for independent variables (ie, condition) and random effects to account for nesting at the therapist level, thereby providing unbiased parameter estimates [154,155]. Nesting at the client level will not need to be controlled in these analyses, as client summed totals will serve as a dependent measure: tallies of sessions attended by family members will be summed across the follow-up period. The LME models package [156] will be used; it provides full information maximum likelihood estimation and restricted maximum likelihood estimation, both of which produce unbiased parameter estimates based on the assumption that data are missing at random and outperform other missing data approaches even when missing at random is not met [157]. Effect sizes will be indexed by η_2_ [158]. However, the nonlinear mixed effects model will be used if the assumption of continuous data is not tenable (eg, when attendance counts are not normally distributed).

*Aim 2b adolescent and family outcomes* analyses will involve similar LME models previously described. To test for change over time, each model will include fixed effects for time (months since baseline, coded as 0, 3, and 6) and random effects for (1) nesting of clients within therapists and (2) repeated measures within person across follow-up. Hypotheses will be tested by adding condition as a fixed effect and examining the condition-by-time interaction on each outcome in separate models. Acknowledging that outcomes may not demonstrate sharp trajectory change during the relatively brief 6-month follow-up window, the intercept will be set at the terminal assessment point by recoding time points (–6, –3, and 0); in doing so, the condition effect for the intercept will reflect a between-group difference at 6-month follow-up. LME modeling is recommended as an alternative to traditional modeling techniques for longitudinal designs with small samples [159].

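### The stated power of 0.80 (0.65) fits a three-occasion average that the plan never tests; the planned Aim 2 tests have about 0.63 to 0.67 (0.48 to 0.51)

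*Protocol article*

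**What the plan says.** Study Power gives one calculation for Aim 2, which it describes as comparing the conditions on family attendance and on client outcomes over time. Its inputs are "Assuming α=.05, a total sample size of N=60 (with 30 clients per condition"), "3 measurement occasions with a moderate intercorrelation" of r=0.50, and d=0.60. On these, "the analysis yields a power of 0.80". At d=0.50 the stated power is 0.65. The section names neither the test nor its sidedness. Study Procedures shows that the three occasions are baseline, 3 months and 6 months.

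Plan of Analyses names the tests:

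- **Aim 2a, attendance:** "tallies of sessions attended by family members will be summed across the follow-up period", so each client contributes one number. The text itself concludes that nesting at client level need not be modelled.
- **Aim 2b, hypothesis test:** time is numeric (0, 3, 6) and hypotheses are tested by "examining the condition-by-time interaction on each outcome in separate models".
- **Aim 2b, second contrast:** time is recoded to end at zero so that "the condition effect for the intercept will reflect a between-group difference at 6-month follow-up".

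**The concern.** A power figure describes one particular test. Three occasions raise power only when the test averages over them. None of the three planned tests does: one uses a single total, one a change over time, and one a difference at the last visit. An average that includes baseline would also be an odd target, because it reaches its stated power only if the conditions already differ by the full d before treatment has had any effect.

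If the planned tests are weaker than stated, a non-significant result will be read as stronger evidence against Fam-AID than it is. The article says that its Aim 2 findings, if promising, will help set the stage for a larger randomized trial, so the sensitivity of those tests matters to its readers.

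**Working it through.** **Inputs.** From Study Power: n=30 per condition, α=0.05, r=0.50, d=0.60 or 0.50. From Study Procedures and Plan of Analyses: occasions at 0, 3 and 6 months. My assumptions: two-sided testing, the same correlation between every pair of occasions, unit SD at each occasion, no dropout and no therapist clustering. The stated calculation mentions neither of the last two.

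**Formula.** For a contrast with variance factor v per client, the noncentrality is δ = d / √(2v/30). Power comes from the noncentral t distribution with 58 df (critical value 2.002).

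**Step 1: reproduce the stated figures.** For the mean of three occasions, v = (1 + 2×0.50)/3 = 0.667.

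- d=0.60: δ = 0.60/√(0.667×2/30) = 2.846, power 0.799.
- d=0.50: δ = 2.372, power 0.645.

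These round to the stated 0.80 and 0.65. No other variant tried gave both. One-sided versions of the planned tests give 0.74/0.61 (attendance, condition-by-time) and 0.77/0.64 (6-month intercept).

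**Step 2: what that test needs.** It has 0.80 only if the difference is 0.60 at baseline too. With differences of 0, 0.60, 0.60 the mean difference is 0.40 and power is 0.46. With 0, 0.30, 0.60 it is 0.30 and power is 0.29.

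**Step 3: the planned tests.**

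*Attendance.* One value per client, v = 1; δ = 0.60/√(2/30) = 2.324.

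*Condition-by-time.* With times 0, 3, 6 the slope weights are (−1/6, 0, 1/6). Six months of slope is therefore the 6-month value minus baseline, with v = 2(1−0.50) = 1. This is the same as attendance.

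*6-month intercept of the linear model.* The fitted 6-month value has weights (−1/6, 1/3, 5/6), and v = 0.50×(1+4+25)/36 + 0.50 = 0.917. With an effect that grows linearly to d, δ = 0.60/√(0.917×2/30) = 2.427.

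| Test | v | Power, d=0.60 | Power, d=0.50 | d for 80% power |
|---|---|---|---|---|
| Mean of three occasions (not planned) | 0.667 | 0.799 | 0.645 | 0.60 |
| Attendance total | 1.000 | 0.628 | 0.478 | 0.74 |
| Condition-by-time | 1.000 | 0.628 | 0.478 | 0.74 |
| 6-month intercept, linear effect | 0.917 | 0.665 | 0.512 | 0.70 |

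At d=0.60, 80% power would need about 45 clients per condition for the first two planned tests and 41 for the intercept.

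**Step 4: sensitivity to the shape of the effect.** If the full d is present at both 3 and 6 months, the attendance and condition-by-time figures do not change. The linear model's 6-month estimate then overshoots: its expected value is (1/3 + 5/6)d = 7d/6, or 0.70 for a true 0.60. Its power becomes 0.795 (0.641 at d=0.50), but that is power for a fitted difference of 0.70, not 0.60.

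**The case against.** **The powered test is inferred.** The article names neither test nor sidedness, so the three-occasion average is my reading. The match on two figures makes it likely but does not prove it. Even one-sided, no planned test reaches 0.80 at d=0.60 under a linear effect. The nearest approach is the two-sided intercept under an immediate, sustained effect (0.795/0.641), which depends on the overshoot in Step 4 and does not help attendance or condition-by-time.

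**The replacement figures are simplified too.** The planned models have therapist random effects, and attendance may be analysed with a nonlinear model. The same therapists appear to treat clients in both conditions, so a therapist intercept could remove variance. With an assumed intraclass correlation of 0.05 to 0.20, v falls to 0.95 to 0.80 and single-value power at d=0.60 becomes 0.65 to 0.72. Dropout, or therapist-by-condition variation, would lower it. This stands as a reason to state the assumptions, but it does not restore 0.80.

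**The correlation could be higher.** At r=0.70 the condition-by-time test would have 0.84. But 0.50 is the article's own value, attendance does not depend on r, and the intercept (linear effect) stays at 0.64 to 0.68 for r from 0.3 to 0.8.

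**Attendance may be covered only by loose wording.** Perhaps so, but the section opens with attendance and gives no other calculation for it.

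**It is a pilot, and it already discloses 0.65 at d=0.50.** It is true that no significance threshold governs the next trial, so the effect on that decision should not be overdrawn. The stated figures are still wrong for the stated tests.

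**Conclusion.** The concern holds. The stated 0.80 and 0.65 correspond to a difference averaged over baseline and both follow-ups, which is not a planned test. At the article's own inputs, attendance and condition-by-time have power of about 0.63 (0.48 at d=0.50), and the 6-month intercept about 0.67 (0.51) when the effect builds linearly. The chance of missing d=0.60 is then 33% to 37%, against the 20% implied.

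The attendance error needs no inference about how the figure was obtained: three correlated occasions cannot apply to an outcome with one value per client. The size of the shortfall rests on two-sided testing, equal correlations of 0.50, no dropout and no therapist clustering. The intercept figure also rests on the linear shape.

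**What to change.** Rewrite Study Power test by test, naming each test and its sidedness:

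- attendance and condition-by-time: 0.63 at d=0.60, 0.48 at d=0.50, detectable d of 0.74;
- 6-month contrast: 0.67 and 0.51, detectable d of 0.70, for an effect that grows linearly.

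Remove attendance from the 0.80 claim, and state the assumptions of equal correlations, no dropout and no therapist clustering. This costs wording only; the stated power becomes less favourable. Sample size and analysis stay as they are.

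If the team wants more power without more clients, a baseline-adjusted contrast is an option but not part of the correction. Adjusted at 6 months, v = 1 − 0.50² = 0.75 gives 0.75 (0.59 at d=0.50). The adjusted mean of 3 and 6 months, v = (1+0.50)/2 − 0.50² = 0.50, gives 0.90 (0.77), but only if the full effect is present at both visits. That would change the analysis text. Because the article describes nonequivalent groups, baseline adjustment and change over time can answer different questions, so the choice should not be made on power alone.

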### Ethical Considerations

Ethics approval for this trial is pending from Solutions Institutional Review Board. Adolescents and caregivers will independently provide informed assent or consent before the initiation of the study activities (Multimedia Appendix 1). All study activities will be subjected to monitoring by the Data Safety and Monitoring Board of the same institution (Multimedia Appendix 2). Any modifications to the protocol that might impact the conduct of the study or its specified objectives and procedures will require a formal amendment to the protocol and approval by the Institutional Review Board and the Data and Safety and Monitoring Board before implementation. As reimbursement for interview completion, each participant receives a gift voucher (of their choice) worth US $110 via Tango Card: US $30 each for participation at baseline and US $40 each for participation during 3-month and 6-month follow-up. All assessment data will be automatically downloaded from the web-based data collection portal into a secure database maintained in a secure firewall- and password-protected location on a data network. All network data are backed up daily. Only project staff will have direct access to the data. All standard procedures for data management and security will be followed. For planned statistical analyses, database managers will extract data from the REDCap repository. All participant identifiers will be removed before the data are provided to statisticians for analysis.

## Results

This study is being conducted over a 3-year period. Participant recruitment and data collection will begin in April 2025. We expect results from this study to be published in 2027.

## Discussion

### Overview

This pilot treatment development study will test feasibility (acceptability and fidelity) and short-term client outcomes (adolescent ID symptoms, adolescent SU, and family communication about SUD+ID) of a modular protocol for addressing cooccurring IDs among adolescents with SU in routine care. Fam-AID will contain 5 modules that can be delivered in any sequence to meet client needs: *family engagement* in treatment planning and services; *relational reframing* of family constraints, resiliencies, and social capital connected to the adolescent’s ID symptoms; *functional analysis* of ID symptoms and related behaviors; *cognitive behavioral therapy* to address ID symptoms and functional needs; and *family psychoeducation and safety planning* focused on education about comorbid SUD+ID and prevention of adolescent self-harm. If shown feasible and effective, Fam-AID will offer a set of pragmatic interventions to SUD clinicians for treating cooccurring IDs in adolescent clients.

Importantly, Fam-AID is not intended to contain components that directly target SUD outcomes. This means that it is designed as an adjunctive intervention to complement and enhance the current SUD interventions, which are already being practiced by a given clinician or agency. The value of adjunctive protocols, such as Fam-AID, is to augment the overall effectiveness of care by addressing prominent cooccurring problems that, if untreated, derail treatment goals for a primary problem. The adjunctive nature of Fam-AID is a key asset for scalability; clinicians are not asked to exchange or markedly alter their base practices for SUD.

Fam-AID contains 5 modules, each consisting of core treatment techniques that have a strong evidence base. In keeping with the principles of modular intervention design [36,160,161], clinicians are invited to select and implement any Fam-AID module, in any order, based on client needs, with a default of delivering them sequentially. The 5 Fam-AID modules are intended to galvanize and reinforce the family support system and equip the adolescent to cope with and ameliorate ID problems. Notably, module 4 draws its menu of core CBT techniques to treat ID-related problems (emotional acceptance, emotional exposure, and behavioral activation) from an existing evidence-based transdiagnostic protocol, which treats the underlying negative affect and emotional dysregulation [77] associated with adolescent IDs. In these ways, Fam-AID is distinct from other adolescent SUD+ID options due to how it combines a core elements strategy, family-focused interventions, and individual CBT techniques, which might enhance the often modest long-term impact of interventions for ID symptoms in usual care [162].

Fam-AID contains 3 additional innovations intended to boost treatment effectiveness for this group identified as highly vulnerable and enhance the feasibility of implementing protocol modules in routine SUD care. First, in line with the core elements strategy, it is intended for use by invested clinicians of any clinical orientation and training background. To be sure, modules 1 and 2 contain techniques drawn from the family therapy approach, whereas modules 3 and 4 techniques derive from CBT. Nevertheless, Fam-AID modules are constructed as basic, step-by-step clinical practice guides that can be adopted and deployed by even entry-level clinicians. Second, it uses evidence-based family engagement techniques to systematically integrate caregivers in the treatment process. Families are not typically centralized in SUD services for adolescents [163] despite the compelling empirical rationale that family-based treatment is a first-line option for adolescent SUD [164], is well established for adolescent depression [165], and is a useful adjunct for adolescent anxiety [166]. Third, it contains a customization feature in which selected CBT techniques are integrated into treatment planning based on a functional ID assessment completed during sessions. In what amounts to a small-scale version of treatment tailoring [66,167], clients and therapists can collaboratively choose which of the 3 CBT techniques (emotional acceptance, emotional exposure, or behavioral activation) is best suited to address the adolescent’s ID symptoms.

### Study Design Limitations and Strengths

Due to the limited number of sites, clinicians, and clients in this study, results will not be generalizable to the broad network of adolescent SUD treatment clinics or SUD clinical workforce. Randomized designs, which provide control against unknown study confounds and allow for reasonable assumptions of causality related to manipulated variables even in small samples, are generally preferable to quasi-experimental interrupted time series designs. However, we decided against using a randomized design for many reasons. It would result in half as many therapists being trained in Fam-AID, which in a small-scale study exacerbates between-therapist variability in protocol fidelity that could dilute proposed effects and reduces therapist generalizability [87,168]. In addition, it introduces the potential for between-condition bleed from training procedures that could nullify protocol effects. In addition, to the degree that usual practices in the study sites (representing the TAU condition) already feature some type of ID-targeted interventions, the interrupted time series design is credibly stringent. This design was also vastly preferred by our partner clinics because it allows all staff to receive Fam-AID training. Importantly, this design can yield hypothesized viability and impact effects even if routine treatment services for SUD are basically inert at either or both study sites.

### Reproducibility and Dissemination Plans

The Fam-AID protocol will be developed to maximize its reproducibility and scalability by featuring a clinically flexible, modular design strengthened by core element techniques. If the study aims are met, the foundation will be laid to test Fam-AID at R01-level scale. Study information and findings will be disseminated through publication of journal articles, presentations at relevant conferences, and reports to relevant stakeholders. If the Fam-AID protocol ultimately demonstrates feasibility and effectiveness, we will use existing state- and national-level clinician training and licensing platforms to ensure the protocol and its companion fidelity tools and procedures are made widely available to agencies and practitioners who serve youth with SUDs.

## Appendix

Multimedia Appendix 1 Sample consent form for this study.

Multimedia Appendix 2 Study committees and teams for this study.

Multimedia Appendix 3 SPIRIT (Standard Protocol Items: Recommendations for Intervention Trials) checklist for this study.

Multimedia Appendix 4 Peer-review report from Interventions to Prevent and Treat Addictions Study Section (IPTA) - Risk, Prevention and Health Behavior Integrated Review Group - Center for Scientific Review (National Institutes of Health, USA).

## Abbreviations

CBT: cognitive behavioral therapy
Fam-AID: Family Support Protocol for Adolescent Internalizing Disorders
HIPAA: Health Insurance Portability and Accountability Act
ID: internalizing disorder
ITT: Inventory of Therapy Techniques
LME: linear mixed effects
REDCap: Research Electronic Data Capture
SU: substance use
SUD: substance use disorder
TAU: treatment as usual
